## Methods/design

### Hypotheses

To investigate the non-inferiority of tTXA to ivTXA in blood conservation and clinical safety, our working hypothesis is that tTXA-treated participants suffer *no more* blood losses or allogeneic transfusions, exhibit *undiminished* postoperative hemoglobin level and coagulation function, and are subject to *no increase* in length of hospital stay (LOH) and adverse event (AE) rate compared with those treated with ivTXA.

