### Sample size and statistical analysis

Our pilot cohort study indicated expected TBLs of 971 ± 459 ml and 911 ± 460 ml respectively in the tTXA and ivTXA groups in lumbar spinal decompression and 3–5 levels of bone graft fusion surgeries. Using PASS version 11.0, a sample size of 70 in each group is calculated to be sufficient with assumed type I error rate α = 0.05, power of test 1 – ß = 0.90, and 20% of TBL (195 ml) set as the non-inferiority cut off. Taking into account a dropout rate of 20%, a sample size of 88 in each group is eventually determined.

All the randomized participants who signed the Informed Consent Form (ICF) and satisfied all inclusion/exclusion criteria and have completed demographic data will be included in the intention to treat (ITT) analysis set. All the participants in the ITT set who have completed the perioperative TBL will be included in the per protocol (PP) analysis set. All the randomized participants who have received at least one dose will be included in the safety analysis (SS) set. All the analyses on efficacy will be based on the ITT set. Analysis on AEs will be based on the SS set.

For the primary outcome TBL, statistical methods for continuous variable analysis will be used in the non-inferiority test in the ITT analysis set, and a sensitivity analysis will be conducted in the PP set. The missing data will be treated as missing at random, and the multiple imputation procedure will be used for the primary outcome. The difference between the tTXA group and ivTXA group will be reported as mean difference and lower one-sided 95% confidence interval (CI), along with a one-sided *p* < 0.025.

For other outcomes, the Kolmogorov-Smirnov statistic with a Lilliefors significance level will be used for testing normality for continuous variables. Continuous variables with normal distribution will be compared using the Student *t* test between groups. The continuous parameters with a skewed distribution will be tested with the non-parametric Mann-Whitney *U* test between groups. The categorical variables will be presented as frequencies and percentages and compared using the chi-square test or Fisher’s exact test. If the total number of cases is less than 40 or the minimum expected count is less than 5, Fisher’s exact test will be used.

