For safety analysis, the AEs and abnormal findings in laboratory tests will be listed with the relationship to the study treatments. Fisher’s exact test will be used to compare the rates of participants who have at least one AE between groups in the SS set.

Statistical analyses will be performed using SPSS version 23.0 software (SPSS Inc., Chicago, IL, USA). A two-sided *p* < 0.05 is considered significant.

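### The primary non-inferiority result pairs a one-sided 95% bound (a 5% test) with one-sided p < 0.025, and on the natural reading the bound named is on the wrong side for blood loss

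*Protocol article*

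**What the plan says.** All of the following is in the Protocol article, mostly under Sample size and statistical analysis.

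- **Primary result.** The tTXA versus ivTXA difference in TBL "will be reported as mean difference and lower one-sided 95% confidence interval (CI), along with a one-sided" p-value threshold of 0.025. The tTXA arm is named first, but no subtraction is written.
- **Margin.** "20% of TBL (195 ml) set as the non-inferiority cut off". No sentence says which confidence limit is compared with it.
- **Planning values.** "expected TBLs of 971 ± 459 ml and 911 ± 460 ml respectively in the tTXA and ivTXA groups".
- **Sample size.** "a sample size of 70 in each group is calculated to be sufficient". The inputs named for this are an alpha of 0.05 and 90% power. The sidedness of alpha is not given. Allowing for 20% dropout, this becomes 88 per group.
- **General level.** The section closes by saying that a two-sided p below 0.05 "is considered significant".
- **Direction of harm.** Under Hypotheses, the working hypothesis is that "tTXA-treated participants suffer *no more* blood losses or allogeneic transfusions" than those given ivTXA.

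**The concern.** One sentence carries the primary conclusion, and two things in it do not fit.

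**Level.** The confidence bound and the p-value are two forms of the same test only if their levels match. Here the bound is at one-sided 5% and the p-value at one-sided 2.5%. A result can meet one and miss the other, and the article does not say which governs. The type I error of the primary claim is therefore 5% or 2.5%, depending on which is read after the data are in.

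**Side.** More blood loss is worse, so inferiority of tTXA is a large positive value of tTXA minus ivTXA. Ruling out an excess of 195 ml needs the upper bound. A lower bound on that difference says nothing about it.

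**Working it through.** **Inputs** (Protocol article, Sample size and statistical analysis): SD 459 ml (tTXA) and 460 ml (ivTXA); expected difference 971 − 911 = +60 ml; margin 195 ml, taken at face value; 70 per group, raised to 88. Let D = mean TBL(tTXA) − mean TBL(ivTXA).

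**The plan's own figures.** The dropout step reproduces: 70 / 0.8 = 87.5, rounded up to 88. The 70 does not. With n = 2·SD²·(z₁₋α + z₁₋β)² / (195 − δ)², pooled SD 459.5 and a t-test correction, 90% power needs:

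| True difference δ (tTXA − ivTXA) | One-sided 0.05 | One-sided 0.025 |
|---|---|---|
| +60 ml | 200 | 245 |
| 0 | 96 | 118 |
| −60 ml | 57 | 70 |

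Exactly 70 also results from δ = 0, one-sided 0.05 and 80% power, which is not the stated power. This bears on the direction question below but is a separate sample-size matter.

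**Standard error at 88 per arm.** SE = √[(459² + 460²)/88] = √(422,281/88) = 69.3 ml, with 174 degrees of freedom.

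**Largest observed D that passes, using the upper bound against +195 ml.**

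- One-sided 95%: 195 − 1.654 × 69.27 = 195 − 114.6 = 80.4 ml.
- One-sided 97.5%, equivalent to p < 0.025: 195 − 1.974 × 69.27 = 195 − 136.7 = 58.3 ml.

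The two criteria disagree for observed D from 58.3 to 80.4 ml. At 70 per arm (SE 77.7 ml) the range is 41.4 to 66.4 ml. Both ranges contain +60 ml.

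**If the trial observes exactly the pilot difference (+60 ml, 88 per arm).**

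- Upper one-sided 95% bound: 60 + 114.6 = 174.6 ml, below 195, so it passes.
- Test against +195 ml: t = (195 − 60)/69.27 = 1.95, one-sided p = 0.0265, so it fails at 0.025.
- Upper one-sided 97.5% bound: 60 + 136.7 = 196.7 ml, which fails, in agreement with the p-value.
- Lower one-sided 95% bound, the one named on the natural reading: 60 − 114.6 = −54.6 ml, which carries no information about +195 ml.

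**How often the criteria disagree (88 per arm).** The probability of passing at a true D of +60 ml is 61.65% at one-sided 0.05 and 49.13% at 0.025, a gap of about 12.5 percentage points. At a true D of 0 the gap is 7.7 points.

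**Which level is the outlier.** For a test in one direction, two-sided 0.05 equals one-sided 0.025. The section's closing statement therefore agrees with p < 0.025. The sample-size alpha of 0.05 fits either level, because its sidedness is not given. Only the one-sided 95% label is out of line.

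**The case against.** **The side error is inferred.** If the difference is meant as ivTXA minus tTXA, non-inferiority is a lower bound above −195 ml, and the lower bound is correct. A lower one-sided interval could also mean one running from minus infinity to an upper limit. Either reading removes the problem. This stands: the article states neither, so the side is wrong on the natural reading and otherwise undefined, but not proven wrong.

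**The plan can still exclude the margin.** A reader might infer that it cannot, or that a clearly worse tTXA would be declared non-inferior. The documents do not support that. The sentence says what will be reported, the same section calls for a non-inferiority test, and a p-value tested against +195 ml would do the job whichever bound is printed. No rule comparing the lower bound with −195 or +195 ml appears in the article, and the Hypotheses section shows that the authors know which direction is harmful.

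**The sample size does not prove a sign reversal.** At the stated 90% power, 70 results when the 60 ml is counted in tTXA's favour, which is suggestive. The zero-difference route with 80% power gives 70 without any reversal.

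**The level may be one mislabelled limit.** The intended 2.5% can be recovered from the neighbouring text, and the bound may be one limit of an ordinary two-sided 95% CI. That is plausible, and it narrows the fault to one label. It does not remove the fault: as written, the two criteria differ, and they differ at the planned result.

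**Conclusion.** The point holds in two parts of unequal certainty.

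1. **Level mismatch: certain from the text.** It survives every reading of the direction. At 88 per arm it produces opposite verdicts for observed excesses of about 58 to 80 ml, including the pilot's +60 ml, with about a 12.5% chance if that is the truth. These figures assume the planned SDs, a two-sample t comparison and all 88 per arm contributing. With 70 per arm the zone moves to about 41 to 66 ml.
2. **Wrong side: holds on the natural reading only.** The reported bound cannot be relied on to show non-inferiority, because neither the subtraction nor the bound to be compared with the margin is stated. A p-value correctly tested against +195 ml could show it.

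The closing two-sided 0.05 is not a further inconsistency. Because this sentence governs the primary conclusion of a non-inferiority trial, it should be corrected before analysis. The Trial status section reports that recruitment was still under way.

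**What to change.** Replace the reporting sentence with an explicit rule:

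- D = mean TBL(tTXA) − mean TBL(ivTXA), with H0: D ≥ +195 ml.
- Non-inferiority is concluded if the upper limit of the two-sided 95% CI for D (one-sided 97.5%) is below +195 ml.
- One-sided alpha is 0.025 for both the interval and the p-value.

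In the sample-size sentence, state the sidedness of alpha and restate the power that follows.

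The wording change is small and needs no new data. The cost lies in what it exposes. At 88 per arm, power at a true difference of +60 ml is about 49% at one-sided 0.025, against 62% at 0.05. At zero difference it is about 80% against 88%. At 70 per arm and +60 ml it is about 41% against 53%. The shortfall from the stated 90% exists at either level, so it should be dealt with as a separate sample-size issue and not used as a reason to keep the looser bound.

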### Participants

Patients aged over 18 years who are classified as American Society of Anesthesiologists (ASA) physical status I–II, diagnosed as having lumbar spinal stenosis/intervertebral disc herniation/spondylolisthesis, requiring lumbar spinal decompression and 3–5 levels of bone graft fusion surgeries will be enrolled in the study after signing a written informed consent.

Patients with past medical history of chronic renal dysfunction (preoperative blood creatinine > 120 mmol/L), liver dysfunction (preoperative blood aspartate aminotransferase (AST) or alanine aminotransferase (ALT) > 50 U/L), coronary artery disease with stent placement, abnormal preoperative coagulation profile (preoperative prothrombin time (PT) elongation > 3 s, activated partial thromboplastin time (APTT) elongation >10 s, platelet counts < 100 × 10^9^/L or > 400 × 10^9^/L, or international normalized ratio (INR) > 1.4), or pre-existing anemia (male < 12 g/dL, female < 11 g/dL), and those who have long-term medications of aspirin and/or other anticoagulants, known allergy to TXA, or religious and/or other beliefs limiting blood transfusion are excluded. Participants who undergo dura mater laceration or unexpected massive bleeding or who receive cell saver application during operation will also be excluded.

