#### Secondary outcomes

Secondary outcomes include:Visible blood losses (intraoperative, postoperative 0–24 h, postoperative 0–48 h, combined perioperative blood loss) and postoperative hidden blood loss (HBL)Postoperative conventional coagulation monitoring indices: PT, APTT, fiber Bragg grating (Fbg), INR, and TEG monitoring indices: reaction time (R time), clot formation time (K time), clot strength (MA), fibrinolysis (LY30)Postoperative hemoglobin nadir (within postoperative 48 h)Perioperative transfusion amounts and ratesPlasma TXA levels tested with solid phase microextraction technique (SPME) [18] 5 min after the last suture (t_4_) and on postoperative day 1 (POD1, t_5_).LOH

Among the preceding indices, combined visible perioperative blood loss refers to the gross visible blood loss since operation initiation until postoperative 48 h. Two pretrained surgeons will take charge of the visible blood loss assessments. Specifically, for intraoperative visible blood loss, it is calculated by weighing surgical sponges, measuring blood collected by suction canisters, and subtracting all irrigations fluids added to the surgical field. For postoperative visible blood losses, since the drainage fluid in the Hemovac includes not only blood but also tissue fluid exudation [19], the actual postoperative blood loss (PBL) will be calculated using our previously reported formula [20]:$$ {\mathrm{PBL}}_{24\mathrm{h}\;\left(48\mathrm{h}\right)}=\mathrm{volume}\ {\mathrm{of}\ \mathrm{drainage}}_{24h\;(48h)}\times {\mathrm{Hct}}_{24\mathrm{h}\left(48\mathrm{h}\right)}/{\mathrm{Hct}}_{\mathrm{ave}} $$where Hct_24h(48h)_ refers to the drainage Hct level tested 24 h or 48 h postoperatively. HBL is also calculated by subtracting the combined visible perioperative blood loss from TBL. All blood losses are determined on the basis of milliliters. If allogeneic transfusion is performed, then TBL is equal to the loss calculated from Hct changes plus the volume transfused.

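### Hemoglobin nadir, PT, APTT and INR are compared without using the preoperative value that eligibility screening supplies, which gives up precision in four secondary comparisons

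*Protocol article*

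**What the plan says.** Four parts of the protocol article bear on this point.

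- **Sample size and statistical analysis.** For all outcomes other than total blood loss, a normality test picks the method: "Continuous variables with normal distribution will be compared using the Student *t* test between groups", otherwise a Mann-Whitney U test. No covariate, change score or baseline adjustment is named for them. The closing lines on analysis set two-sided 0.05 as the significance level.
- **Secondary outcomes.** The endpoints are postoperative levels: "Postoperative hemoglobin nadir (within postoperative 48 h" and "Postoperative conventional coagulation monitoring indices: PT, APTT, fiber Bragg grating (Fbg), INR".
- **Participants.** The exclusions include "abnormal preoperative coagulation profile (preoperative prothrombin time (PT) elongation > 3 s, activated partial thromboplastin time (APTT) elongation >10 s", an INR limit of 1.4, "or pre-existing anemia (male < 12 g/dL, female < 11 g/dL". None of these can be applied without a preoperative measurement.
- **Hypotheses.** With topical TXA, "postoperative hemoglobin level and coagulation function" are expected to be undiminished compared with intravenous TXA.

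Randomization is 1:1 in blocks of 4, with no stratification factor named.

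**The concern.** A postoperative hemoglobin or clotting value partly reflects where the patient started. Differences between patients in starting level therefore enter an unadjusted comparison as noise, and any chance difference in baseline between the arms carries into the estimated treatment difference in proportion to the correlation. The baseline values exist, and the stated analysis ignores them. With no stratification named, only chance balances these baselines.

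At stake is the width of the intervals on four secondary comparisons that support the working hypothesis. Wider intervals make a real difference between the routes, in either direction, harder to see. The primary outcome is not involved: total blood loss is computed from each patient's own preoperative and day-3 hematocrit.

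This is not a gap that an unseen analysis plan would be expected to fill, because the protocol names the tests and they are unadjusted.

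**Working it through.** **Inputs.** From the protocol: 70 per group before dropout, 20% dropout, 88 per group enrolled, 1:1 allocation, two-sided 0.05. Assumed, because the protocol does not give it: the correlation rho between preoperative and postoperative values, taken as 0.3, 0.5 and 0.7. Differences are in units of the outcome's SD.

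**The plan's own figure.** The protocol states no precision or power for these secondary outcomes. The only figure used here is the enrolled number: 70 / (1 − 0.20) = 87.5, rounded up to 88, which reproduces. The 70 is taken as given; its derivation concerns the primary outcome and does not bear on this point.

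**Precision.** The unadjusted standard error is sqrt(2/n): 0.151 SD at 88 per group and 0.169 SD at 70. ANCOVA multiplies the variance by (1 − rho²) and the standard error by sqrt(1 − rho²). The unadjusted 95% half-width at 88 per group is 1.96 × 0.151 = 0.295 SD. The number per group that the unadjusted test would need to match ANCOVA with 88 is 88 / (1 − rho²).

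| rho | variance reduction | SE factor | half-width at 88 (0.295 unadjusted) | unadjusted n to match 88 |
|---|---|---|---|---|
| 0.3 | 9% | 0.954 | 0.282 SD | about 97 |
| 0.5 | 25% | 0.866 | 0.256 SD | about 117 |
| 0.7 | 49% | 0.714 | 0.211 SD | about 173 |

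**Power.** Take the difference that the unadjusted t test detects with 80% power: 0.425 SD at 88 per group, 0.477 SD at 70. In the normal approximation this is (1.960 + 0.842) = 2.802 standard errors. Adjusted power is Φ(2.802 / sqrt(1 − rho²) − 1.960):

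- rho 0.3: Φ(0.98) = 83.6%
- rho 0.5: Φ(1.28) = 89.9%
- rho 0.7: Φ(1.96) = 97.5%

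The gain reaches 5 percentage points at rho of about 0.355. The 80% is only a benchmark, since the protocol powers total blood loss alone.

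**Chance imbalance.** At 88 per group, 95% of chance baseline differences lie within ±1.96 × 0.151 = ±0.295 SD. An imbalance at that edge moves the unadjusted difference by rho × 0.295. At rho 0.5 this is 0.148 SD, about one standard error (0.151 SD).

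Given a baseline imbalance of k standard errors and no treatment effect, the unadjusted z statistic has mean rho × k and SD sqrt(1 − rho²). At rho 0.5:

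- k = 1.96: (1.96 − 0.98) / 0.866 = 1.13, giving a conditional false-positive rate of about 12.9%.
- k = 0: 1.96 / 0.866 = 2.26, giving about 2.4%.

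Averaged over all possible imbalances, the rate is the nominal 5%.

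**The case against.** The strongest reply is that nothing in the plan is invalid. A randomized comparison of postoperative values is unbiased and holds its 5% error rate over randomizations. That is correct, and it limits this point to efficiency. The 12.9% above is the unfavourable tail of a conditional rate and must not be read as the error rate of the planned test.

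A reader might infer that undiminished means relative to each patient's own starting level, so that the unadjusted test answers the wrong question. The protocol does not support this. The Hypotheses section sets the comparison against patients given intravenous TXA, and the endpoint is a level, not a fall.

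A reader might also infer that adjustment would let the trial conclude that hemoglobin or coagulation is undiminished. It would not. No margin is stated for these outcomes, and a non-significant two-sided test does not show absence of harm, whether adjusted or not.

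The size of the gain rests wholly on an assumed correlation, and there are reasons it could be low. The exclusions narrow the baseline range of all four measures. The Discussion's limitations note that postoperative transfusion and oral intake vary between patients and may affect hematocrit, and this could also loosen the link between preoperative hemoglobin and the nadir. Nor need the coagulation indices behave like hemoglobin. All of this stands, so the result is shown as a range.

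The case for going beyond the four outcomes is weaker. The exclusions name no preoperative Fbg or thromboelastography value, and Fig. 1 could not be consulted. Sex-specific anemia limits govern eligibility; they do not show that sex still predicts the nadir once baseline hemoglobin is in the model.

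What survives is narrow: baselines that already exist are left out of an analysis that the protocol spells out.

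**Conclusion.** The point holds as an efficiency improvement for four secondary outcomes: hemoglobin nadir, PT, APTT and INR. The planned unadjusted tests are valid but less precise than the data allow, and they leave each estimate exposed to whatever baseline imbalance chance produces. The figures rest on an assumed correlation of 0.3 to 0.7 and a linear relation between baseline and outcome. At 0.3 or below the benefit is modest (under 4 points of power from an 80% benchmark); at 0.5 it equals about 29 more patients per group (117 against 88). It is most plausible for hemoglobin. The documents do not show that any stated conclusion would change.

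**What to change.** In the section on sample size and statistical analysis, before unblinding, make the main comparison for hemoglobin nadir, PT, APTT and INR an ANCOVA of the postoperative value on treatment group and the same measure's preoperative value. Report the adjusted difference with its 95% CI. Use a log transform or robust standard errors for skewed indices, and keep the planned t or Mann-Whitney test as supportive. Extend the model to Fbg and the thromboelastography indices only if preoperative values are collected. Adding sex to the hemoglobin model is optional.

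The cost is a change of wording and about one degree of freedom per covariate. No new measurement is needed for the four outcomes. The small downside is that skewed indices are then summarised by a mean or geometric-mean difference instead of a rank comparison. Any claim that hemoglobin or coagulation is undiminished would still need its own prespecified margin.

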### Trial registration, ethical aspects, and informed consent

The study proposal and study materials were approved by the institutional review board (IRB) of Peking Union Medical College Hospital (PUMCH). The study is registered at ClinicalTrials.gov (NCT03011866). When significant modification occurs, we will inform the investigators, all participants, and the trial registry. The investigators will obtain informed consent from each participant before they enter the study. Personal information about the enrolled participants will be safely and confidentially kept, and the anonymized individual patient data will be shared on request.

### Dissemination plan

Results of the trial will be submitted to an international peer-reviewed journal. The results will also be presented at national and international conferences relevant to the subject fields.

## Discussion

It is widely acknowledged that the complexity of multisegmental spinal decompression and bone graft fusion surgery positively correlates with perioperative blood losses. In such surgical arenas, significant blood transfusions are often required, with additional risks of infectious disease transmission, coagulation dysfunctions, and postoperative spinal epidural hematoma formation [21] inevitably introduced. Since ivTXA has been testified as efficacious in reducing blood losses and transfusions in a series of complex surgeries [2, 3, 22], it has also been routinely adopted in spinal surgeries across medical centers.

However, concerns remain over the theoretical thrombogenicity [23] and propensity for convulsive seizures by the use of ivTXA [2, 24]. To settle such concerns, local and more targeted delivery of the drug may provide a promising alternative for blood conservation in spine surgeries while minimizing patients’ systemic exposure to TXA. Currently, the efficacy of tTXA has been well established in major surgeries, especially in hip and knee arthroplasty [12, 14, 25–28]. Yet, clinical research regarding tTXA application in spinal surgeries has been scarce. In a placebo-controlled study, Krohn et al. investigated the impact of tTXA on postoperative blood loss in patients undergoing lumbar instrumented spinal fusion surgery [29]. The wound was irrigated with tTXA for 5 min before removal of excess fluid and wound closure. The postoperative blood loss was reduced by half in patients receiving the treatment, demonstrating the hemostatic efficacy of tTXA. Nevertheless, principal limitations reside in both the quite limited sample size and the placebo-controlled study design; thus, no definite conclusion should be drawn on the comparative hemostatic efficacy of tTXA and ivTXA. Therefore, the present TARGETS study with sufficient sample size will investigate for the first time whether tTXA conveys non-inferior efficacy in managing gross hemorrhage and transfusions compared with ivTXA. With the results of the TARGETS study, we expect to provide high-quality clinical evidence for the role of tTXA in perioperative blood conservation, thereby optimizing the delivery route of TXA in spinal surgeries.

While visible blood losses are well recognized and researched, the invisible HBL is relatively overlooked, largely due to its residual in dead spaces and extravasation into tissues. However, according to previous studies, both ours and others’, quantities of HBL in spine surgeries are substantial. Smorgick et al. reported that HBL accounted for 39–42% of TBL in primary/revision posterior spinal fusion surgeries [30], and a retrospective study conducted at our center reported the percentage as high as 47% [19, 31]. HBL has been reported as significantly associated with increased postoperative complications and LOH [32]; therefore, it constitutes a crucial component of the enhanced recovery after surgery (ERAS) scheme. Since there has been no study investigating the effect of tTXA on HBL, the issue will be investigated for the first time in this TARGETS study, with the hope that the study results will provide solid evidence for constructing the ERAS scheme in the spinal surgery field.

In the present study, thromboelastography (TEG) will be adopted for real-time evaluation of the coagulation system. By utilizing this dynamic functional hemostatic test, alterations in R time, K time, MA, and LY30 during the coagulation and lytic phases can be identified with minimal delay [33]. Combining the point-of-care (POC) TEG results and the systemic TXA levels revealed by the SPME technique [18], the potential rationale of tTXA on perioperative coagulation function will be precisely depicted, thereby attesting to the hemostatic efficacy as well as the safety profile of tTXA.

The strength of this study is that, for the first time, a prospective, randomized, double-blind, head-to-head study design with sufficient sample size will be adopted to investigate the clinical non-inferiority of tTXA to ivTXA in multisegmental spinal decompression and bone graft fusion surgeries. The results of this study will provide high-quality clinical evidence for the hemostatic efficacy and safety of tTXA application, thereby optimizing the TXA delivery route and the ERAS scheme in spinal surgeries.

There are possible limitations of the TARGETS study. Firstly, there may be concerns that wound irrigation with TXA solution might introduce inconsistent drug delivery doses within the surgical site. However, Ker et al. [34] have found that doses of tTXA administered in RCTs were highly heterogeneous (ranging from 0.7 mg to 100 mg/ml of saline solution), while the hemostatic effect was not dose-dependent. Secondly, as per previous studies, both by our team and others [20, 30], Hct level on POD3 is considered to reach a steady state as the patients are assumed hemodynamically stable, and it is thus adopted for calculating TBL. However, both postoperative transfusions and oral intake may vary with each individual patient, which may exert different effects on the Hct levels. To further establish tTXA as a promising blood conservation strategy in spinal surgeries, larger multicenter investigations are still expected.

